## 2.6 - Human Studies of Intracerebral Administration of Platinum Agents

A variety of drug delivery systems has been proposed for the treatment of patients with malignant gliomas to deliver anti-cancer drugs locally in a sustained slow-release manner [[20](#_ENREF_20), [21](#_ENREF_21), [33](#_ENREF_33), [50](#_ENREF_50)]. To the best of our knowledge, there are only two clinical reports describing the direct i.c. infusion of platinated drugs for glioma treatment. Bouvier et al.[[26](#_ENREF_26)] infused 8.2 mg of cisplatin over 10 days into the left frontoparietal lobe of a patient with a recurrent malignant glioma using 68 catheters in clusters of four, each catheter connected to an Alzet^TM^ pump (121 µg of cisplatin per catheter). There were no adverse side effects associated with catheter implantation, chemotherapy, or catheter removal. Although chemotherapy halted progression of the tumor, it recurred, and the patient died 6 months after treatment[[26](#_ENREF_26)]. The only evidence of tissue damage was an infiltrate of foamy macrophages and foreign body giant cells that were reacting to microscopic fragments of bone. Contiguous brain showed gliosis, but no evidence of hemorrhage. Although this was not really CED, it resulted in higher drug concentrations than otherwise would have been obtainable by systemic administration, and provides one data point demonstrating that direct infusion of platinated drugs can be performed safely.

In the other study involving 17 patients with glioblastoma (GBM), Sheleg et al.[[23](#_ENREF_23)] administered cisplatin, incorporated into biodegradable polymers into the cavity created following subtotal resection of the tumor. Twenty polymer discs (1.5 x 1.5 cm^2^), each loaded with 1 mg/cm^2^ of cisplatin, were placed in the cavity created following resection of the tumor. Two weeks after surgery, the patients received radiotherapy (2 Gy per fraction for a total dose of 60 Gy). An additional 21 patients with GBM only received radiotherapy. As shown by brain CT, it was determined that complete biodegradation of the cisplatin containing discs had occurred by 4-5 weeks following their placement in the tumor bed. The combined treatment significantly increased (p=0.00001) the median survival time (427 d.) compared to that observed in GBM patients who had received radiotherapy alone (211 days). Although, there was no autopsy data to indicate what, if any, neuropathologic changes had occurred in the treated patients, clinically the treatment seemed to have been well-tolerated.

# 3 - Pharmaceutical Information

The carboplatin infusion will be prepared by the OSUMC / James Pharmacy Investigational Drug Service. Carboplatin will be received from their pharmacy wholesaler as a sterile, lyophilized powder which is stable at room temperature until the expiration date on the bottle. OSUMC / James Pharmacy will dissolve the carboplatin in 0.9% sodium chloride using aseptic techniques to the concentration desired based on the cohort level. The final infusate will be an isotonic solution received in syringes which is stable for 24 hours.

Carboplatin [diammine(1,1-cyclobutanedicarboxylato-(2)-0,0’) platinum, NSC 241240, IND 19,314] (CBDCA). It is a cyclobutane dicarboxylate derivative of the potent antitumor platinum II compound, DCCP. Several studies into the mechanism of action of platinum II compounds have compared the biochemical reactivities of *cis* and *trans* stereoisomers as the latter have virtually no antitumor activity; differences in reactivities therefore help elucidate the mechanism(s) of activity of the *cis* compounds. Both *cis* and *trans* compounds form inter-(DNA-DNA, DNA-protein) and intrastrand crosslinks, and both react with phosphate but not sugar groups of DNA. Only *cis* compounds, however, show preferential reactivity with G-C base pairs. The primary lesion formed with bidentate platinum compounds such as CDDP and CBDCA, as a result of this reaction, is an intrastrand cross-link between two adjacent guanines; interstrand crosslinks are relatively rare. Physically, the association with both CDDP and CBDCA with DNA has been found to induce a “premelting” effect in intact DNA, characterized by a weakening or rupture of hydrogen bonding between bases and resulting in an opening of the double helix. A DNA shortening effect has also been seen. In contrast, *trans* compounds cause the formation of single stranded, denatured DNA. Carboplatin is a highly effective anti-cancer drug that have been used clinically to treat a variety of malignancies[[12](#_ENREF_12)]. The formation of platinum adducts with DNA can interfere with the repair of radiation-induced damage, which could explain the synergistic interaction between either cisplatin or carboplatin and ionizing radiation, which have been observed in the F98 rat glioma model[[16](#_ENREF_16), [35](#_ENREF_35), [36](#_ENREF_36)].

# 4 - Patient Eligibility Criteria

4.1 - Population:

Patients, aged 18 to 70, with grade III or IV astrocytoma (anaplastic astrocytoma or glioblastoma), or grade III oligodendroglioma or oligastrocytoma (anaplastic oligodendroglioma or anaplastic oligoastrocytoma) at first or second recurrence are eligible to enroll in this protocol. Subjects are required to have radiographic confirmation of disease progression and a Karnofsky Performance Status of at least 60. Eligible patients must be at least 6 weeks out from last dose of nitrosoureas, bevacizumab and other antiangiogenic therapies, 8 weeks out from completion of radiotherapy (fractionated or stereotactic), and 4 weeks out from last dose of other cytotoxic chemotherapies. Patients cannot be receiving other investigational agents and must be on a stable dose of dexamethasone for ≥1 week prior to baseline MRI. The tumor progression must be amenable to craniotomy for resection. Candidates for the study include only those patients for whom craniotomy for tumor resection is recommended as treatment for their tumor progression.

## 4.2 - Inclusion Criteria

- All patients must have progressive disease for which craniotomy and tumor resection is recommended as treatment.
- All patients must sign a consent form indicating that they are aware of the investigational nature of the study. The informed consent form will indicate that the patient has been made aware of all other appropriate therapies.
- Patients with histologically confirmed grade III or IV astrocytoma, oligoastrocytoma, and oligodendroglioma who are at first or second recurrence
- All patients require an initial diagnosis of a malignant glioma as outlined in the inclusion criteria which must be confirmed at the treating facility.
- Patients must have unequivocal evidence of tumor progression by MRI performed no longer than 28 days prior to study registration.
- Patients must have pathologically confirmed recurrence at the time of catheter placement.
- Patients must be on a stable or decreasing dexamethasone dosage for at least 1 week prior to baseline MRI.
- Patients must have been treated previously with radiation therapy and treatment must have been completed at least 8 weeks prior to surgery for catheter implantation
- Last dose of cytotoxic chemotherapy must have been at least 4 weeks (6 weeks for nitrosoureas) prior to catheter placement. Patients are eligible if they received bevacizumab or other anti-VEGF therapies, although the most recent dose must be at least 6 weeks prior to catheter placement.
- Patients previously treated with stereotactic radiosurgery, stereotactic radiotherapy, brachytherapy, Gliadel wafers or other intratumoral chemotherapy are eligible.
- Patients must have recovered from all prior therapy.
- Age ≥ 18 and ≤70 years of age
- Patients must have a life expectancy of ≥ 3 months and a Karnofsky performance status ≥ 60.
- Patients must have normal organ and marrow function as defined below:
  - leukocytes >3,000/mcL
  - absolute neutrophil count >1,500/mcL
  - platelets >100,000/mcL
  - hemoglobin >9 g/dL
  - serum calcium <12.0 mg/dL
  - total serum bilirubin < institutional ULN
  - AST(SGOT)/ALT(SGPT) ≤2.5 X institutional ULN
  - creatinine <1.5 X institutional ULN
- Women of child bearing years must have a negative pregnancy test (serum or urine) within 1 week of study entry. Men and women of reproductive potential must agree to use an effective contraceptive method including one of the following: surgical sterilization (tubal ligation for women or vasectomy for men); approved hormonal contraceptives (such as birth control pills, Depo-Provera or Lupron Depro); barrier methods (such as condom or diaphragm) used with a spermicide cream or an intrauterine device (IUD).
- Patient or designated individuals with durable medical power of attorney must give written informed consent prior to any study-specific procedures being implemented.
- Both men and women and members of all races and ethnic groups are eligible for this trial.

## 4.3 - Exclusion criteria

- Patients with infratentorial, multifocal, or pathologically confirmed CSF disseminated tumor.
- Patients that have been treated with > 3 prior chemotherapy regimens
- Pregnant or lactating women or women of childbearing potential and men who are sexually active and not willing/able to use medically acceptable forms of contraception.
- Patients who have a history of bleeding disorders including congenital or acquired coagulopathies
- Known AIDS based upon current CDC definition or other acquired or congenital disorder of the immune system.
- Patients with unstable or serious concurrent illness including, but not limited to, ongoing or active infections requiring IV antibiotics or psychiatric illness/social situations that would limit compliance with study requirements are ineligible. (If patient has a stable chronic infection requiring oral antibiotics, the patient may be treated at the investigators discretion; however a clinical note must include the justification regarding the safety of treating the patient)
- Patients who have received any other investigational agent in a 28-day period prior to enrollment in this study.
- Patients whose tumors are located less than 2 cm from the ventricles.
- Patients taking greater than 12mg daily of dexamethasone.
- Prior invasive malignancy that is not low-grade glioma, glioblastoma or gliosarcoma (except non-melanomatous skin cancer or carcinoma in situ of the cervix) unless the patient has been disease free and off therapy for that disease for a minimum of 3 years

# 5 - Treatment Plan

5.1 - Study Design:

Phase I dose escalation study

5.2 - Proposed trial:

Carboplatin in a volume of 54 ml will be administered intracerebrally by convection enhanced delivery at a flow rate of 0.75 ml/hr over 72 hr. The first patient will receive an initial starting dose of 2 µg over 72 hrs (0.667 µg/24 hr). This first patient will be observed for 28 days after completion of the infusion, prior to enrollment of additional patients. In the absence of dose-limiting toxicity (DLT), 3 more patients will be entered at the next higher dose level, which will be double the prior dose (i.e., 4 µg over 72 hrs). If 1of 3 patients exhibits DLT, an additional 3 patients will be entered at that dose level. Dose escalation will continue until DLT occurs in at least 2 out of 6 patients. The maximum tolerated does (MTD) will be defined as the highest dose level at which 3/3 or 5/6 patients could be treated without DLT. Dosage escalation will proceed in subsequent cohorts of 8 µg, 16 µg, 32 µg, 64 µg, 85 µg, 107 µg and 128 µg. If the MTD has not been reached, we will submit a request to the FDA with a schedule for continued escalation until DLT is reached. If 2 of 3 patients demonstrate DLT at 2 µg, the dose will be reduced to 1 µg for the next three patients. DLTs are defined, in the presence of supportive care, as any Grade 3 or 4 toxicity that is possibly, probably, or definitely related to the study drug. The maximum tolerated dosage is defined as the dose level below that causing DLT in at least two patients. The length of the DLT window will be at least 28 days, and this time interval must elapse before completion of one cohort and initiation of the next.

5.3 - Population:

Patients, aged 18 to 70, with grade III or IV astrocytoma (anaplastic astrocytoma or glioblastoma), or grade III oligodendroglioma or oligastrocytoma (anaplastic oligodendroglioma or anaplastic oligoastrocytoma) at first or second recurrence are eligible to enroll in this protocol. Subjects are required to have radiographic confirmation of disease progression and a Karnofsky Performance Status of at least 60. Eligible patients must be at least 6 weeks out from last dose of nitrosoureas, bevacizumab and other antiangiogenic therapies, 8 weeks out from completion of radiotherapy (fractionated or stereotactic), and 4 weeks out from last dose of other cytotoxic chemotherapies. Patients cannot be receiving other investigational agents and must be on a stable dose of dexamethasone for ≥1 week prior to baseline MRI. The tumor progression must be amenable to craniotomy for resection. Candidates for the study include only those patients for whom craniotomy for tumor resection is recommended as treatment for their tumor progression.

5.4 - Outline of Treatment Plan – details below the outline

- Pre-operative assessment for enrollment in clinical trial (see above)
  - Tumor board confirms that the patient is an appropriate candidate for the clinical trial based on diagnosis and radiographic evidence of recurrent disease
    - Inclusion criteria met (see list above)
    - Exclusion criteria met (see list above)
  - The clinical trial is fully explained to the patient including all risks of the clinical trial and informed consent is obtained
- Surgery
  - Surgery occurs in the operating room at OSU Main Hospital
  - There are multiple objectives of surgery:
    - The tumor is surgically removed
    - Intraoperative frozen section confirms high grade glioma
    - Infusion catheters (2-4) are inserted into the brain around the tumor resection cavity
- Post-operative admission – hospitalization after surgery occurs in the OSU Main Hospital
  - patient is admitted to the ICU for the first 24 hours after surgery during which time the following occurs:
    - Monitoring for adverse events occurs continuously during hospitalization
    - vital signs and neurologic assessment hourly
    - CT to assess catheter placement
    - Labs as per study calendar (see below)
    - Neurologic assessment by neurosurgeon ([name]) and resident house staff daily
    - Neurologic monitoring by RN as per ICU standard of care
    - Once the CT scan has confirmed catheter placement, carboplatin infusion begins
      - management of carboplatin infusion by surgical team as directed by attending neurosurgeon ([name])
      - Carboplatin infusate is supplied in a syringe at a concentration determined by the dosing algorithm described above
      - Syringe placed in infusion pump that controls infusion rate
      - Syringe connected to infusion catheters via infusion tubing
      - Each syringe contains 24 hours of infusate
      - Syringe is changed at 24 and 48 hours
      - Total infusion time is 72 hours
  - After 24 hours in the ICU, the patient is transferred to the ward in the James if the patient is stable for transfer to the ward
    - Carboplatin infusion continues for a total of 72 hours
    - Daily neurologic assessment by neurosurgeon ([name]) and resident house staff
    - Routine neurologic and vital signs assessment by RN as per standard of care and at least every 4 hours
    - Daily labs as per study protocol (see below)
  - Catheter removal at bedside after infusion completed – catheters are removed in a similar fashion as standard ventricular catheters. A member of the neurosurgical team as directed by the neurosurgical attending will remove each catheter and place a stitch in the scalp at the exit point of the catheter
  - An MRI to assess for residual tumor will be performed after the catheters are removed
  - Discharge from hospital as per standard of care – discharge criteria after brain tumor resection will be met prior to discharge home
- After discharge home
  - Serial imaging, labs and neurologic assessments as per study calendar (see below)

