## 5.12 - Dosage escalation plan

The starting dose of carboplatin will be 2 µg. The carboplatin dose will be escalated in cohorts of 3 (maximum of 6 patients in each dose level if DLT occurs). Three patients will be entered first at Dose Level 1. In the absence of DLT, 3 more patients will be entered at the next higher dose level. If 1of 3 patients had DLT, an additional 3 patients will be entered at that dose level. Dose escalation will continue until DLT occurs in at least 2 out of 6 patients. The MTD will be defined as the highest dose level at which at least 5/6 patients could be treated without DLT. If 2 of 3 patients in Dose Level 1 demonstrate DLT, the next cohort of patients will receive Dose Level 0. At least 28 days must elapse between completing enrollment in a cohort level and beginning treatment at the next cohort level.

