## 5.13 - Dose-Limiting Toxicity (DLT)

DLTs are defined, in the presence of supportive care, as any Grade 3 or 4 toxicity that is possibly, probably, or definitely related to the study drug. The maximum tolerated dosage is defined as the dose level below that causing DLT in at least two patients. The length of the DLT window will be at least 28 days, and this time interval must elapse before completion of one cohort and initiation of the next.

Non-hematologic toxicities such as rash, nausea, vomiting and hypertension will only be considered DLTs if they remain grade 3 or greater despite maximal medical therapy 72 hours after maximal medical therapy is initiated. The first deep venous thrombosis or pulmonary embolism will not be considered a DLT because these complications are common among patients with high-grade gliomas. Patients who develop DVT and/or PE may receive anticoagulation therapy and resume the clinical trial once clinically stable. A second DVT or PE on optimal medical therapy will be considered a DLT.

| **Number of Patients with DLT**  **At a Given Dose Level** | **Escalation Decision Rule** |
| --- | --- |
| 0 out of 3 | Enter 3 patients at the next dose level |
| > 2 | Dose escalation will be stopped. This dose level will be declared the maximally administered dose (highest dose administered). Three (3) additional patients will be entered at the next lowest dose level if only 3 patients were treated previously at that dose. |
| 1 out of 3 | Enter at least 3 more patients at this dose level.   - If 0 of these 3 patients experience DLT, proceed to the next dose level. - If 1 or more of this group suffer DLT, then dose escalation is stopped, and this dose is declared the maximally administered dose. Three (3) additional patients will be entered at the next lowest dose level if only 3 patients were treated previously at that dose. |
| <1 out of 6 at highest dose level below the maximally administered dose | This is generally the recommended phase 2 dose. At least 6 patients must be entered at the recommended phase 2 dose. |

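### Protocol section 5.2 opens 4 µg after one DLT-free patient at 2 µg, whereas sections 5.12 and 5.13 require three patients at that level

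*Protocol*

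**What the plan says.** Section 5.2 of the Protocol assigns the 2 µg starting dose to the first patient only. It continues: "This first patient will be observed for 28 days after completion of the infusion, prior to enrollment of additional patients". The next step is: "In the absence of dose-limiting toxicity (DLT), 3 more patients will be entered at the next higher dose level", and the same sentence identifies that level as double the prior dose, 4 µg. No sentence in 5.2 enters a second or third patient at 2 µg. Later in the paragraph a step-down rule begins "If 2 of 3 patients demonstrate DLT at" and completes the condition with 2 µg.

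Section 5.12 escalates in cohorts of three, expandable to six. It states: "Three patients will be entered first at Dose Level 1". It does not mention a single first patient followed alone. Its step-down rule is: "If 2 of 3 patients in Dose Level 1 demonstrate DLT, the next cohort of patients will receive Dose Level 0".

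The decision table in section 5.13 has two routes upward. With 0 DLTs in 3 patients the instruction is "Enter 3 patients at the next dose level". With 1 DLT in 3, three more are added at the same level, and "If 0 of these 3 patients experience DLT, proceed to the next dose level". There is no row for one patient.

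**The concern.** If the first patient has no DLT, a site following 5.2 opens 4 µg next. A site following 5.12 and 5.13 treats two more patients at 2 µg first. These are conflicting instructions for the first escalation decision, and that decision feeds the primary endpoint in section 8.1 (DLT and MTD).

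The likely intent is a sentinel patient within a cohort of three, because the 2-of-3 rule in 5.2 makes little sense otherwise. No section says so: 5.12 omits the sentinel, and 5.2 omits the rest of the Level 1 cohort.

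The microgram dose is low, but Level 1 still carries procedural risk. Every level infuses 54 mL over 72 hours through intracerebral catheters. Section 8.1 counts toxicity attributable to the drug or the protocol as DLT, and also grade 2 intracranial haemorrhage. A DLT in the first patient is therefore possible whatever the drug dose.

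**Working it through.** The protocol states no DLT rate and no operating characteristics, so there is no figure of its own to reproduce.

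**1. Patients needed at 2 µg before 4 µg opens, if no DLT occurs**

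- Section 5.2 read literally: 1.
- Section 5.12 and the 5.13 table: 3.

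**2. What the literal reading leaves without a rule**

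- *DLT in the first patient.* The text below the 5.13 table adds three patients when one patient at a level has a DLT. That gives 1 + 3 = 4 patients. The table covers 3 and 6, so there is no row for going up on 1 of 4.
- *Two DLTs at 4 µg.* 2 µg then becomes the MTD under section 5.13, with one patient treated there. The backfill of three is conditional on exactly three having been treated before. Even if it is applied, 1 + 3 = 4 falls short of the six patients that 5.13 requires at the MTD.

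**3. Chance of escalating from 2 µg to 4 µg**

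Let p be the true DLT rate at 2 µg. All values of p are assumptions.

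- A, the 3+3 rule of 5.12 and 5.13: (1−p)³ + 3p(1−p)²·(1−p)³ = (1−p)³ + 3p(1−p)⁵
- B, literal 5.2, assuming a first-patient DLT blocks escalation: 1−p
- C, literal 5.2, with three patients added after a first-patient DLT and escalation if none of them has a DLT: (1−p) + p(1−p)³

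For example, at p = 0.30: A = 0.343 + 0.9 × 0.168 = 0.494; B = 0.700; C = 0.700 + 0.3 × 0.343 = 0.803.

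| p | A | B | C | B − A (points) | C − A (points) |
|---|---|---|---|---|---|
| 0.05 | 0.973 | 0.950 | 0.993 | −2.3 | +1.9 |
| 0.10 | 0.906 | 0.900 | 0.973 | −0.6 | +6.7 |
| 0.20 | 0.709 | 0.800 | 0.902 | +9.1 | +19.4 |
| 0.30 | 0.494 | 0.700 | 0.803 | +20.6 | +30.9 |
| 0.40 | 0.309 | 0.600 | 0.686 | +29.1 | +37.7 |

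**4. What a clean result tells us**

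With 0 DLTs in n patients, the exact one-sided 95% upper bound on the DLT rate is 1 − 0.05^(1/n). For n = 1 it is 95%; for n = 3 it is 63%.

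**5. Scale of the drug dose**

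Section 5.12.2 scales the rat dose to 33 µg/g × 600 g = 19,800 µg per human hemisphere. The starting dose is 1/9,900 of that (19,800 / 2), and 4 µg is 1/4,950 (19,800 / 4).

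**The case against.** The strongest reply is that a compatible reading exists. Section 5.2 does not say at which dose the additional patients enrol after the 28-day hold, nor that absence of DLT is judged on the first patient alone. One could treat one patient at 2 µg, wait, add two at 2 µg, and then enter three at 4 µg without breaking any sentence. The disputed sentence also appears almost word for word in 5.12, where it follows a cohort of three. This does not remove the problem: the reading supplies a step that no section states, and 5.2 moves directly from the single patient to a named 4 µg.

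Other points stand in part:

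- The 2-of-3 rule in 5.2 presupposes three patients at 2 µg and does not mandate them. The explicit requirement is in 5.12 and the 5.13 table.
- Stopping rules are framed by count (two patients with DLT), so two DLTs among four patients does have a stated consequence. The gap is going up on 1 of 4.
- Section 5.13 requires six patients at the MTD, so 2 µg could not properly be declared the MTD on one patient. The backfill rule would not reach six, however. From 4 µg upward both readings use three patients, expandable to six.
- The largest difference, 38 points, needs a 40% DLT rate at the planned starting dose together with the add-three rule. Nothing in the protocol suggests such a rate. At 5% to 10%, version B is marginally stricter than the 3+3.

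**Conclusion.** The contradiction holds and should be corrected before the first escalation decision is made. Most of the text points to three patients at 2 µg, but the one sentence that describes the first escalation gives one.

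The effect on the chance of escalating depends on assumed DLT rates. It is between −2 and +7 points at 5% to 10%, and between +9 and +38 points at 20% to 40%, where the spread also reflects what is assumed after a first-patient DLT. Expected drug-related harm at 2 µg is probably small, and the conflict directly affects only the 2 to 4 µg step. It matters because the rule for that step cannot be determined from the document, and because the literal route reaches cases that the 5.13 rules do not cover.

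**What to change.** Put the same text in sections 5.2 and 5.12, for example:

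> Three patients will be treated at Dose Level 1 (2 µg). The first is followed for 28 days from the end of the infusion before the second is enrolled, and counts as one of the three; two more are then treated at 2 µg. Escalation, or expansion to six, follows the table in section 5.13, and a DLT in the first patient counts as one of the three.

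In 5.2, delete the step that goes to 4 µg after the first patient. Keep the Level 0 rule in both sections, worded as two or more of three patients with DLT at Level 1 sending the next three to 1 µg, because the 5.13 table has no Level 0 row.

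Counting a first-patient DLT as one of three is a design choice that matches the 3+3. Under this wording the hold gives time to assess the first patient but does not by itself stop enrolment at 2 µg. If the sponsor wants a first-patient DLT to have a stricter consequence, this text is the place to state it.

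Cost: wording only. Relative to 5.12, it adds one 28-day wait after the first patient. Relative to literal 5.2, it adds two patients at 2 µg and at least one further wait. The earliest start of 4 µg moves from about day 31 (3 + 28) to about day 62 (2 × 31) after the first infusion begins. That assumes the second and third patients are treated together and the second wait also runs from the end of infusion. Section 5.12 counts its 28 days from completion of cohort enrolment, which could make the wait slightly shorter.
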